#### MOST Framework

Telehealth intervention studies typically use randomized controlled trial designs. However, telehealth interventions are comprehensive packages that include components such as coaching calls, educational content, texting, email, and mobile apps. Randomized controlled trials fail to reveal which components are responsible for any behavior change elicited during the intervention; rather, they only show whether the intervention package as a whole had any effect. Therefore, it is necessary to know which elements of telehealth interventions are needed or should be removed for a more efficient telehealth intervention. To optimize the My Health, My Life, My Way program, the MOST framework will be used to assess which study elements (coaching calls and gamification) elicit behavior change. The MOST framework, derived from engineering principles, is an efficient method to gather information on each intervention component or package and investigate whether the presence or absence of a component has an impact on the performance of other components [20,21,27]. Within this study, we will assess coaching calls (scheduled or on demand) and gamification (scaled rewards or flat rewards).

### Intervention Design

The My Health, My Life, My Way study is a 2 × 2 randomized factorial experiment. By using the MOST framework, we can evaluate the effectiveness of different combinations of features within the My Health, My Life, My Way program, such as fixed versus gamified rewards and scheduled versus on-demand coaching calls. Eligible participants will be randomly assigned to one of four groups: (1) scheduled coaching calls with gamified rewards, (2) scheduled coaching calls with rewards independent of gamification, (3) no scheduled coaching calls with gamified rewards, and (4) no scheduled coaching calls with rewards independent of gamification (Table 1). For the study, 4 weeks is considered a month, thereby making the study duration 24 weeks. Study activities involving participants with disabilities will be conducted primarily on the web nationally in the United States.

**Table 1 table1:** Research design.

Gamified rewards	Coaching calls	
	Scheduled coaching calls	No scheduled coaching calls
Gamification-based rewards	Scheduled coaching calls with gamified rewards	No scheduled coaching calls with gamified rewards
Rewards independent of gamification	Scheduled coaching calls with rewards independent of gamification	No scheduled coaching calls with rewards independent of gamification

### Sample Size

We will use a 2 × 2 factorial design for this MOST trial (detailed in the Intervention Design subsection). Our sample size and power calculations for the primary outcome (health-related quality of life) assume an overall 2-sided type I error rate of 5%, 80% power, and an analysis of covariance–based approach with 2 independent dichotomous factors (ie, each factor has 2 levels). We will assume an attrition rate of 20%, with 160 (80%) participants completing the study (referred to as completers) from 200 participants enrolled. Under these assumptions, we will have 80% power to detect at least a minimally detectable difference (Cohen *d*) of 0.36 for the main effect or 0.18 in terms of the standardized regression coefficient. In these calculations, we assume a conservative correlation of 0.6 between the baseline covariate and outcome, which is similar to that in a previous study by Froehlich-Grobe et al [4]. In addition, 12 participants will be enrolled for pilot-testing the My Health, My Life, My Way program [28].

### Recruitment

Recruitment will be conducted on the web nationally through the National Center on Health, Physical Activity and Disability (NCHPAD) website and its associated social media. The NCHPAD website has approximately 45,000 site visits per month, with most of the internet traffic flowing from the United States (74%). Through these mechanisms, interested individuals will be directed to a website landing page that will have promotional media content and information about the study. From here, participants will be directed to a separate link through the Health Insurance Portability and Accountability Act (HIPAA)–compliant REDCap (Research Electronic Data Capture; Vanderbilt University) platform [29,30] and complete a screening eligibility form. If deemed eligible, the participants will be sent an electronic consent form to be completed using REDCap. On the basis of our recruitment methods, we expect that approximately 400 individuals will be screened for eligibility.

### Allocation

Participants will be randomized into 1 of 4 study arms in a 1:1:1:1 allocation ratio using a computer-generated randomization procedure. The allocation sequence will be implemented after the baseline survey is completed. The computer-generated randomization process will be implemented in REDCap after the data from the baseline survey are completed using REDCap. This will trigger the allocation procedure to randomly assign participants to 1 of the 4 study arms. The health coach will be notified about the randomization through the telecoaching dashboard and will inform the participants about their randomization into the My Health, My Life, My Way intervention or the attention control arm during the orientation call.

### Blinding (Masking)

The principal investigator and primary statistician will be blinded to the randomization of the participants into the study arms. All other study staff will be unblinded for purposes of recruitment, consent, orientation calls, welcome calls, and coaching calls. There are no circumstances in which the principal investigator or statistician will become unblinded during this protocol.

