### Overview of the Intervention

#### Orientation Call

After the welcome call and randomization, a study health coach will be notified through REDCap that a participant has been randomized to one of the study arms and will conduct an orientation call with the participant. The purpose of this call by the health coach is to introduce themselves to the participants as their primary health coach and to schedule the first weekly coaching call. For those not receiving scheduled coaching calls, the health coach will inform participants that they can contact the coaching staff during the study to ask questions related to the educational content provided on the platform.

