### Participant Study Activities

#### Gamification Component

All participants, regardless of gamification variation, will be able to obtain points and badges on the platform. Participants can check their points status at any time during the study by logging in to the platform to view an itemized list for all badges and points. In addition, participants will be provided email notifications for all gamification updates. All activities, such as viewing and reading educational content and logging in to the platform, will automatically be updated on the platform. Health coaches will encourage participants to engage on the platform regularly. Those not receiving scheduled coaching calls who exercise the on-demand coaching option will be encouraged by a health coach to use the platform regularly.

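### Coaches learn each participant's reward level without needing it, and the same coaches encourage the platform use that earns points

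*Protocol article*

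**What the plan says.** **Who is blinded.** Under Blinding (Masking), "The principal investigator and primary statistician will be blinded to the randomization of the participants into the study arms". The next sentence covers everyone else: "All other study staff will be unblinded for purposes of recruitment, consent, orientation calls, welcome calls, and coaching calls".

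**What the coach is told.** The Orientation Call section states that "a study health coach will be notified through REDCap that a participant has been randomized to one of the study arms". The Allocation section adds: "The health coach will be notified about the randomization through the telecoaching dashboard and will inform the participants about their randomization". It names the telecoaching dashboard as the channel where the Orientation Call section names REDCap.

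**What an arm is.** Intervention Design defines each arm by both factors, for example "1) scheduled coaching calls with gamified rewards, (2) scheduled coaching calls with rewards independent of gamification".

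**What the coach does.** The orientation call is described thus: "The purpose of this call by the health coach is to introduce themselves to the participants as their primary health coach and to schedule". What gets scheduled is the initial weekly call. Later calls cover educational content on nutrition, physical activity and medication adherence. On-demand contacts cover questions about that content.

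**How rewards run.** In the Gamification Component section, activities are recorded by the platform without staff action, participants can look up their own points and badges, and "participants will be provided email notifications for all gamification updates".

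**Encouragement.** The same section says: "Health coaches will encourage participants to engage on the platform regularly". It extends this to on-demand users in the arms without scheduled calls. The Gamification section lists logging in and using the content among the activities that count as participation. In the gamified level, points grow the longer participation is kept up.

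**The concern.** A coach has to know whether a participant has scheduled calls. The coach does not have to know whether that participant's points escalate or stay flat. The design gives the coach both facts and also asks the coach to promote the behavior on which the rewards act. A coach who knows that points are escalating might press harder to keep a run going. A coach who knows that they are flat might press harder to compensate. Either response would be counted as an effect of gamification.

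Contact is concentrated in the scheduled-call arms: one call a week for 24 weeks, so up to 24 calls of up to 60 minutes, in about half of the 200 participants. Differential encouragement there would affect the gamification main effect and would also look like an interaction between calls and rewards, which the factorial design is meant to estimate. Participants know their own rewards and the survey outcomes are self-reported. Coach behavior is therefore one of the few sources of bias on this factor that the design can still control.

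**Working it through.** **1. Does the coach learn the reward level?** No single sentence says so. It follows from three statements taken together:
- Blinding (Masking): staff other than the two named roles are unblinded, coaching calls included.
- Orientation Call: the coach is notified of randomization to one of the arms.
- Intervention Design: an arm is a coaching level combined with a reward level.

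Nothing in the article withholds the reward level from the coach.

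**2. Does any stated coach task need it?**

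| Task | Needs coaching level | Needs reward level |
|---|---|---|
| Orientation call: introduction, scheduling or explaining on-demand access | Yes | No |
| Weekly content calls | Yes | No |
| On-demand content questions | Yes | No |
| Encouraging platform use | No | No |
| Recording activity, notifying points | Done by platform and email | Not a coach task |

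**3. The plan's own precision.** Inputs from Sample Size: 160 completers, two-sided 5% error rate, 80% power, baseline correlation 0.6. Each factor compares 80 with 80.
- Residual SD = sqrt(1 − 0.6²) = 0.8.
- SE of a main effect = 0.8 × sqrt(2/80) = 0.126 SD.
- Detectable difference = (1.960 + 0.842) × 0.126 = 0.354 by the normal approximation, and 0.357 by noncentral t with 155 df.

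The stated 0.36 is reproduced. Power at 0.36 is 81.2% (normal) or 80.7% (t).

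**4. How a coach-induced bias would enter.** Let G1 be the gamified-minus-flat contrast in the scheduled arms and G0 the same contrast in the other arms.
- Main effect = (G1 + G0)/2.
- Interaction contrast = G1 − G0.

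If coach behavior adds b to G1 only, the main effect shifts by b/2 and the interaction contrast by b. With 40 completers per cell, the SE of the interaction contrast is 0.8 × sqrt(4/40) = 0.253, twice that of the main effect. The two shifts are therefore equal in standard-error units.

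**5. Illustration only.** The document gives no value for b. The values below are assumptions.

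| Assumed b (SD) | Main-effect shift | Shift / SE | Type I error for gamification |
|---|---|---|---|
| 0 | 0 | 0 | 5.0% |
| 0.10 | 0.05 | 0.40 | 6.8% |
| 0.20 | 0.10 | 0.79 | 12.4% |

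If the bias runs the other way (coaches compensate flat-reward participants) with size 0.10, power at a true 0.36 falls to Φ((0.36 − 0.05)/0.126 − 1.960) = 69%, from 81%.

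**The case against.** **Safeguards exist.** Calls follow a prepared content outline. Encouragement is described without reference to reward level. The Auditing section lists call logs, audio recordings and checklists reviewed at regular intervals. This stands in part, because these measures lower the risk. None of them masks the coach, however, and none requires encouragement to be the same across reward levels.

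**It may be synergy rather than bias.** The MOST Framework section wants to know whether one component changes how another performs. Coaches who reinforce escalating rewards could be part of the package as delivered. That reading is coherent, but the Gamification section asks whether gamification features by themselves change motivation and engagement. Coach knowledge of the reward level blurs that question.

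**The size is conjecture.** This stands. The primary outcome is SF-36E quality of life at 6 months. Differential encouragement would first have to change platform use, and platform use would then have to change quality of life. Engagement measures are more directly exposed. The illustrative figures only restate the assumed b. Larger figures would follow if participants without scheduled calls were equally exposed, but their contact with coaches is optional, so the documents do not support that.

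**Stronger readings that a reader might infer.**
- *Coaches must announce the reward level.* The Allocation section has the coach tell participants their assignment, but the sentence goes on to describe that assignment as the intervention or an attention control arm. It does not mention rewards.
- *Coaches can see participants' points.* The article describes only participants viewing their own.
- *Staff know allocations at recruitment, consent or the welcome call.* Allocation is triggered only once the baseline survey is complete, so none exists at recruitment or consent. No arm-dependent task is described for the welcome call. Changing that list would alter nothing the trial does.

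**A condensed article may omit screen details.** It may, but this article states positively that staff are unblinded for coaching calls and that the coach is notified of the arm.

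**Conclusion.** The point holds as a low-cost improvement. As the sections combine, coaches know the reward level, no stated task needs it, and they promote the behavior it rewards. The resulting bias is possible and has not been demonstrated. It would fall mainly in the scheduled-call arms and would affect the gamification contrast and the interaction. Its size cannot be derived from the document; only its form can (b/2 on the main effect, b on the interaction contrast). That form assumes the bias is confined to the scheduled arms and that completers are spread evenly over the four cells. It does not affect the sample size calculation, which reproduces.

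**What to change.** 1. Have both notices to coaches (REDCap and telecoaching dashboard) show only whether calls are scheduled or on demand.
2. Deliver the reward terms to participants by automatic platform message and email.
3. Use identical wording for coach encouragement of platform use at both reward levels, and check it with the call logs and recordings already listed under Auditing.
4. State in Blinding (Masking) that coaches are masked to reward level. If the sponsor wants coaches to know it, say so, and define the gamification effect as including coach awareness.

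Separately, reconcile the reference to an attention control arm in the Allocation section with the 2 x 2 design.

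The cost is a display setting, an automatic message and a few lines of text. Sample size, power and analysis are unchanged. Masking will be partial because participants may mention their rewards on calls.

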### Eligibility Criteria

Eligible participants must meet the following inclusion criteria: (1) aged ≥18 years; (2) self-reported diagnosis of heart disease, chronic lung disease, hypertension, or type 2 diabetes; (3) living with a permanent physical disability such as spinal cord injury, spina bifida, multiple sclerosis, or stroke; (4) speak and read English; and (5) availability of a smartphone or computer. To screen for permanently impaired mobility, we will use the National Health and Nutrition Examination Survey (NHANES; physical functioning) [31].

The exclusion criteria are as follows: (1) current enrollment in any structured intervention, (2) severe cognitive impairment, (3) major cardiac event in the past 12 months, (4) resting tachycardia, (5) renal failure, (6) severe peripheral neuropathy, (7) active treatment for cancer in the past 12 months, and (8) having both visual and hearing impairments (either is acceptable).

### Participant Timelines and Intervention Duration

The study duration for those enrolled in the study will be 6 months (24 weeks), regardless of study arm allocation. Participants assigned to groups with scheduled coaching calls will receive scheduled weekly coaching calls. Those assigned to a group without scheduled coaching calls will have access to health coaches during the study and be able to communicate with the health coaches as needed.

### Study Survey Packets

After enrolling in the study, participants will automatically be electronically delivered a REDCap link to a survey packet. This survey packet will include demographics and outcome measures (Table 2). Participants will be asked to complete this survey packet 3 times during the 6-month study period (excluding the demographics in the first survey packet). The surveys should take approximately 20 minutes to complete at each time point. The time points include baseline, 3 months, and 6 months.

**Table 2 table2:** Measures of effectiveness.

Variables^a^	Instruments	Time points
Health-related quality of life	Enabled version of 36-item Short Form Health Survey (primary outcome)	Baseline, 3 months, and 6 months
Physical activity	Godin Leisure-Time Exercise Questionnaire	Baseline, 3 months, and 6 months
Physical activity	Minutes, steps, and related data from Fitbit	Continuous
SE^b^ for managing symptoms	PROMIS^c^ Item Bank v1.0–Self-Efficacy for Managing Chronic Conditions–Managing Symptoms–Short Form 4a	Baseline, 3 months, and 6 months
SE for managing daily activities	PROMIS Item Bank v1.0–Self-Efficacy for Chronic Conditions–Managing Daily Activities–Short Form 4a	Baseline, 3 months, and 6 months
SE for managing sleep disturbance	PROMIS Item Bank v1.0–Sleep Disturbance–Short Form 4a	Baseline, 3 months, and 6 months
Psychosocial Illness	PROMIS Item Bank v1.0–Psychosocial Illness Impact-Positive–Short Form 8a	Baseline, 3 months, and 6 months
SE for managing emotions	PROMIS Item Bank v1.0–Self-Efficacy for Managing Chronic Conditions–Managing Emotions–Short Form 4a	Baseline, 3 months, and 6 months
SE for managing social interactions	PROMIS Item Bank v1.0–Self-Efficacy for Managing Chronic Conditions–Managing Social Interactions–Short Form 4a	Baseline, 3 months, and 6 months
Emotional distress	PROMIS Item Bank v1.0–Emotional Distress-Depression–Short Form 4a	Baseline, 3 months, and 6 months
SE for managing medications and treatments	PROMIS Item Bank v1.0–Self-Efficacy for Managing Chronic Conditions–Managing Medication and Treatment–Short Form 4a	Baseline, 3 months, and 6 months
SE for managing sleep-related impairments	PROMIS Short Form v1.0–Sleep-Related Impairment–Short Form 4a	Baseline, 3 months, and 6 months
Dietary intake	Short Healthy Eating Index	Baseline, 3 months, and 6 months
Medication adherence	Medication Adherence Rating Scale and Beliefs About Medication Questionnaire	Baseline, 3 months, and 6 months
Usability	Health Information Usability Evaluation Scale and System Usability Scale	Three months and 6 months

^a^In addition to the variables listed in the table, primary care visits, pharmacy visits, physical therapy and occupational therapy visits, emergency visits, and hospitalizations in the last 3 months (self-reported) will also be taken into account.

^b^SE: self-efficacy.

^c^PROMIS: Patient-Reported Outcomes Measurement Information System.

### Welcome Call

After the first survey packet is electronically delivered to participants, study team members will contact the participants by telephone. The purpose of this call is to welcome them into the program and explain the program elements. During the call, the staff will inform the participants that they will receive a technology package in the upcoming days.

### Randomization

A randomization sequence will be generated and stored within REDCap, which assigns a participant to 1 of the 4 study arms of the My Health, My Life, My Way study. Randomization will occur only after the baseline survey packet is complete.

### Overview of the Intervention

#### Orientation Call

After the welcome call and randomization, a study health coach will be notified through REDCap that a participant has been randomized to one of the study arms and will conduct an orientation call with the participant. The purpose of this call by the health coach is to introduce themselves to the participants as their primary health coach and to schedule the first weekly coaching call. For those not receiving scheduled coaching calls, the health coach will inform participants that they can contact the coaching staff during the study to ask questions related to the educational content provided on the platform.

#### Intervention Package

All participants, regardless of study arm allocation, will receive an intervention package that will include a PA tracker (Fitbit; Google LLC) and access to a telehealth platform. The Fitbit tracker will be shipped to the participants after randomization. The telehealth platform will be a central location for educational content (videos, articles, etc) for participants to access during the study. Those with conversational agents (eg, Amazon Echo) will be provided access to a My Health, My Life, My Way specific program that can operate with their home device. This package will be used for intervention delivery and not for outcome measurements.

#### Educational Content and Health Coaching for the Study Arms

The study arms for the My Health, My Life, My Way study with the coaching calls for all groups will be guided by a prepared outline of inclusive educational content that will be delivered to the participants through the telehealth platform. This content will be delivered at the beginning of each week. The educational content will be created and adapted for individuals with physical disabilities by experts and delivered to the participants as multimedia content. There will be generalized educational content applicable to all participants. On the basis of a specific physical disability as well as specific health conditions, education-specific content will be tailored to each individual. For those receiving scheduled coaching calls, the content discussed will include nutrition and eating habits, exercise and PA, and medication adherence. Questions outside the scope of the health coaching content will be dealt with by the study clinician. If the study team determines that the questions indicate that it is necessary to collect a participant’s detailed medical profile, the participant will be guided to communicate with their primary care physician. Finally, the health coach will address other health-related questions that the participant may have. For each call, the health coach will be able to record notes on the telehealth platform regarding topics discussed with the participant for future calls, as needed.

